## CONSORT 2010 checklist of information to include when reporting a randomised trial\*

| Section/Topic                    | Item No | Checklist item                                                                                                                                                                              | Reported on page No |
|----------------------------------|---------|---------------------------------------------------------------------------------------------------------------------------------------------------------------------------------------------|---------------------|
| Title and abstract        |         |                                                                                                                                                                                             |                     |
|                                  | 1a      | Identification as a randomised trial in the title                                                                                                                                           | 1                   |
|                                  | 1b      | Structured summary of trial design, methods, results, and conclusions (for specific guidance see CONSORT for abstracts)                                                                     | 3                   |
| Introduction              |         |                                                                                                                                                                                             |                     |
| Background and objectives        | 2a      | Scientific background and explanation of rationale                                                                                                                                          | 4-6                 |
|                                  | 2b      | Specific objectives or hypotheses                                                                                                                                                           | 6                   |
| Methods                   |         |                                                                                                                                                                                             |                     |
| Trial design                     | 3a      | Description of trial design (such as parallel, factorial) including allocation ratio                                                                                                        | 13                  |
|                                  | 3b      | Important changes to methods after trial commencement (such as eligibility criteria), with reasons                                                                                          | N/A                 |
| Participants                     | 4a      | Eligibility criteria for participants                                                                                                                                                       | 13-14               |
|                                  | 4b      | Settings and locations where the data were collected                                                                                                                                        | 13                  |
| Interventions                    | 5       | The interventions for each group with sufficient details to allow replication, including how and when they were actually administered                                                       | 14-15               |
| Outcomes                         | 6a      | Completely defined pre-specified primary and secondary outcome measures, including how and when they were assessed                                                                          | 15-17               |
|                                  | 6b      | Any changes to trial outcomes after the trial commenced, with reasons                                                                                                                       | N/A                 |
| Sample size                      | 7a      | How sample size was determined                                                                                                                                                              | 18                  |
|                                  | 7b      | When applicable, explanation of any interim analyses and stopping guidelines                                                                                                                | 18                  |
| Randomisation:            |         |                                                                                                                                                                                             |                     |
| Sequence generation              | 8a      | Method used to generate the random allocation sequence                                                                                                                                      | 14                  |
|                                  | 8b      | Type of randomisation; details of any restriction (such as blocking and block size)                                                                                                         | 14                  |
| Allocation concealment mechanism | 9       | Mechanism used to implement the random allocation sequence (such as sequentially numbered containers), describing any steps taken to conceal the sequence until interventions were assigned | 14                  |
| Implementation                   | 10      | Who generated the random allocation sequence, who enrolled participants, and who assigned participants to interventions                                                                     | 14-15               |

|                                                      |     |                                                                                                                                                   |                              |
|------------------------------------------------------|-----|---------------------------------------------------------------------------------------------------------------------------------------------------|------------------------------|
| Blinding                                             | 11a | If done, who was blinded after assignment to interventions (for example, participants, care providers, those assessing outcomes) and how          | 14                           |
|                                                      | 11b | If relevant, description of the similarity of interventions                                                                                       | 14                           |
| Statistical methods                                  | 12a | Statistical methods used to compare groups for primary and secondary outcomes                                                                     | 18                           |
|                                                      | 12b | Methods for additional analyses, such as subgroup analyses and adjusted analyses                                                                  | N/A                          |
| Results                                       |     |                                                                                                                                                   |                              |
| Participant flow (a diagram is strongly recommended) | 13a | For each group, the numbers of participants who were randomly assigned, received intended treatment, and were analysed for the primary outcome    | 6                            |
|                                                      | 13b | For each group, losses and exclusions after randomisation, together with reasons                                                                  | Figure 1                     |
| Recruitment                                          | 14a | Dates defining the periods of recruitment and follow-up                                                                                           | 6                            |
|                                                      | 14b | Why the trial ended or was stopped                                                                                                                | N/A                          |
| Baseline data                                        | 15  | A table showing baseline demographic and clinical characteristics for each group                                                                  | Table 1                      |
| Numbers analysed                                     | 16  | For each group, number of participants (denominator) included in each analysis and whether the analysis was by original assigned groups           | 6                            |
| Outcomes and estimation                              | 17a | For each primary and secondary outcome, results for each group, and the estimated effect size and its precision (such as 95% confidence interval) | 7-9                          |
|                                                      | 17b | For binary outcomes, presentation of both absolute and relative effect sizes is recommended                                                       | 7-9                          |
| Ancillary analyses                                   | 18  | Results of any other analyses performed, including subgroup analyses and adjusted analyses, distinguishing pre-specified from exploratory         | 7
Figure 3                |
| Harms                                                | 19  | All important harms or unintended effects in each group (for specific guidance see CONSORT for harms)                                             | 9                            |
| Discussion                                    |     |                                                                                                                                                   |                              |
| Limitations                                          | 20  | Trial limitations, addressing sources of potential bias, imprecision, and, if relevant, multiplicity of analyses                                  | 12                           |
| Generalisability                                     | 21  | Generalisability (external validity, applicability) of the trial findings                                                                         | 9-12                         |
| Interpretation                                       | 22  | Interpretation consistent with results, balancing benefits and harms, and considering other relevant evidence                                     | 9-12                         |
| Other information                             |     |                                                                                                                                                   |                              |
| Registration                                         | 23  | Registration number and name of trial registry                                                                                                    | 13                           |
| Protocol                                             | 24  | Where the full trial protocol can be accessed, if available                                                                                       | Supplementar
y Appendix 1 |
| Funding                                              | 25  | Sources of funding and other support (such as supply of drugs), role of funders                                                                   | 26                           |

\*We strongly recommend reading this statement in conjunction with the CONSORT 2010 Explanation and Elaboration for important clarifications on all the items. If relevant, we also recommend reading CONSORT extensions for cluster randomised trials, non-inferiority and equivalence trials, non-pharmacological treatments, herbal interventions, and pragmatic trials. Additional extensions are forthcoming: for those and for up to date references relevant to this checklist, see [www.consort-statement.org](http://www.consort-statement.org).

## **GLOSSARY**

|        |                                             |
|--------|---------------------------------------------|
| ADR    | adverse drug reaction                       |
| AE     | adverse event                               |
| ANCOVA | analysis of covariance                      |
| ANOVA  | analysis of variance                        |
| BP     | blood pressure                              |
| CDS    | Compound Danshen                            |
| CHD    | coronary heart disease                      |
| CMH    | Cochran-Mantel-Haenszel                     |
| CSC    | clinical study coordinator                  |
| CRF    | case report form                            |
| DMC    | Data Monitoring Committee                   |
| DQF    | data queries form                           |
| ECG    | electrocardiogram                           |
| FAS    | full analysis set                           |
| HDL    | high density lipoprotein                    |
| LDL    | low density lipoprotein                     |
| LOCF   | last observation carried forward            |
| MDS    | multidimensional scaling analysis           |
| NONMEM | nonlinear mixed effect model                |
| PPS    | per protocol set                            |
| SAQ    | Seattle Angina Questionnaire                |
| SAE    | serious adverse event                       |
| SAP    | stable angina pectoris                      |
| SDA    | similarity degree analysis                  |
| SFDA   | State Food and Drug Administration of China |
| SOP    | standard operating procedure                |
| SS     | safety analysis set                         |
| TCM    | traditional Chinese medicine                |
| WM     | western medicine                            |

## **SUMMARY OF CHANGES**

**Summary of Changes for ChiCTR-TRC-09000332, Efficacy and Safety of Xinxuekang Capsule in the Treatment of Angina Pectoris Associated with Coronary Heart Disease (Blood Stasis Syndrome): A Multi-Center, Randomized, Parallel-Controlled, Double-Blind, Adaptive Clinical Trial**

**All changes in this version appear in boldface and italic type. Major changes include the following:**

- 1) In Section 3.2, A total of 576 study participants with angina pectoris was planned initially. After the interim analysis, the sample size was re-estimated to be 736.**
- 2) In Section 3.3, After the sample size was expanded to 736 patients, the final case assignment in 4 participating sites also changed (184 patients in each site; 92 in the trial group and 92 in the control group).**

## PROTOCOL SYNOPSIS

---

### TITLE:

Efficacy and safety of Xinxuekang capsule in the treatment of angina pectoris associated with coronary heart disease (blood stasis syndrome): A multi-center, randomized, parallel-controlled, double-blind, adaptive clinical trial (superiority design)

---

### DESIGN:

A multi-center, randomized, parallel-controlled, double-blind, adaptive clinical trial (superiority design)

---

### NUMBER OF SITES:

4 sites

---

### SAMPLE SIZE:

A total of 576 study participants with angina pectoris was planned initially. ***After the interim analysis, the sample size was re-estimated to be 736.***

---

### POPULATION:

Patients aged 40 to 70 years who suffered from stable effort angina, CCS angina class I, II or III with an attack frequency equal to or greater than 2 episodes per week were eligible for inclusion in the study.

---

### RANDOMIZATION:

Randomization to XXK capsule or CDS tablet will be in a 1:1 ratio

---

### REGIMEN:

Trial group: XXK capsule + placebo of CDS tablet, oral, 2 capsules + 2 tablets a time, 3 times a day;

Control group: CDS tablet + placebo of XXK capsule, oral, 2 tablets + 2 capsules a time, 3 times a day.

---

### TREATMENT DURATION:

20 weeks treatment.

---

### OUTCOME MEASURES:

Efficacy:

---

---

The primary efficacy endpoint of this study is:

- Proportions of patients who were angina-free.
- Proportion of effective electrocardiogram (ECG) improvement.

Secondary efficacy endpoints are:

- Change from baseline in weekly average frequency of self-reported angina episode over the 20-weeks treatment phase.
- Weekly average nitroglycerin consumption rate at week 8 and week 20.
- Change from baseline in 5 dimensions of the Seattle Angina Questionnaire (SAQ)

and the proportions of patients who were clinical significance at week 8 and week 20.

- Change from baseline in the blood stasis syndrome and the proportion of patients who had significant syndrome improvement.
- Change from baseline in ECG exercise test (the first 1/3 of patients included at each site) performed at 0 and 8 weeks.
- Change from baseline in serum lipid: total cholesterol, triglyceride, HDL cholesterol, and LDL cholesterol, measured at 0 and 8 weeks.
- Related signs: heart rate, rhythm, murmur, and BP, recorded before and after

Treatment.

- Accompanying symptoms after treatment: fatigue, shortness of breath, aversion to cold, cold extremities and etc. (recorded as “yes” or “no”).

Safety:

- Vital signs;
  - Blood, urine and stool routine tests;
  - Liver function (ALT), kidney function (BUN and Cr);
  - Any AE that occurs throughout the treatment period.
-

## **1. BACKGROUND INFORMATION**

Xinxuekang (XXK), an oral capsule, is a pure traditional Chinese medicine (TCM) preparation manufactured by modern scientific techniques. It is indicated for the treatment of angina pectoris associated with coronary heart disease (blood stasis syndrome or “Xueyu zheng”), which has the functions of promoting blood circulation, removing blood stasis, promote qi circulation and relieving pain. It has been approved by the State Food and Drug Administration of China (SFDA) and widely used to treat angina in Chinese medical practice for many years.

Pre-clinical studies of XXK capsule mainly include pharmacokinetic, pharmacodynamic and toxicological (acute and chronic toxicities) studies, which are summarized in separate brochures.

## **2. OBJECTIVES**

To investigate the clinical pharmacological characteristics of XXK capsule in the treatment of angina associated with coronary heart disease (blood stasis syndrome).

- To evaluate the efficacy of XXK capsule versus Compound Danshen (CDS) tablets in the treatment of angina associated with coronary heart disease (blood stasis syndrome) by analyzing the proportions of patients who were angina-free, changes in the frequency, intensity and duration of angina, use of nitroglycerin, electrocardiogram (ECG) readings, changes in the SAQ and TCM syndrome transformation;
- To evaluate the efficacy of XXK capsule versus CDS tablets in the treatment of angina associated with coronary heart disease (blood stasis syndrome) by analyzing changes in blood coagulation, lipid and hemorheological parameters;
- To evaluate the safety of XXK capsule in the treatment of angina associated with coronary heart disease (blood stasis syndrome) by analyzing changes in blood (RBC, Hb, PLT, WBC, N, and L), urine and stool routine tests, liver (ALT) and kidney (BUN and Cr) functions before and after treatment, the frequency and incidence of adverse events (AEs) during treatment as well as their relationship to the study drug.

## **3. STUDY DESIGN**

### **3.1 Superiority design**

An adaptive design is applied in this clinical trial, which utilizes accumulating data to modify aspects of the study as it continues, without undermining the validity and integrity of the trial. “Validity” refers to deducing correct statistical analysis without comprising the bias that might include protecting the Type I error; and “integrity” refers to preplanning, as much as possible, based on intended adaptations, maintaining confidentiality of data, and providing convincing results to a broader scientific community.

This study aims to evaluate the efficacy and safety of XXK capsule versus CDS tablets in the treatment of angina associated with coronary heart disease (blood stasis syndrome).

Four qualified study sites will be recruited to conduct the trial.

Due to the adaptive design, one interim analyses is planned. If the superiority of the trial group is demonstrated at the time of interim analysis, then the trial should be terminated, which is also satisfies the ethical considerations.

### **3.2 Sample size**

#### **Initial estimation of sample size**

Since this trial adopts an adaptive design, we initially estimated the sample size based on one of the primary efficacy endpoints, i.e. the proportions of patients who were angina-free according to findings from other and previous studies[1-2]. We assume that the effective rate in the proportions of patients who were angina-free of the trial group was 30%, while that of the control group was 20%. We chose a significance level of 0.05 and a target test power of 0.80. The trial is planned to enroll 465 patients. Considering the dropout rate and stratified block based on the site, the sample size is enlarged to 576 and one planned interim analyses by a Data Monitoring Committee (DMC) will be performed after 288 patients enrolled. Enrollment will be suspended if XXK capsule is found to be significantly more efficacious than the CDS tablets and the O’Brien–Fleming spending function according to the method of Lan and Demets will be applied.

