### 6.2 Efficacy parameters

The primary efficacy endpoint of this study is:

- Proportions of patients who were angina-free.

Angina-free was defined as the responses of patients' anginal symptoms were "none" on the Quantification Score of Angina Pectoris (see page 19 for details) including three dimensions (attack frequency, severity and duration of angina) over the 20-weeks treatment phase. The Quantification Score of Angina Pectoris comprising questions investigating the patients' anginal symptoms was administered by the physician in charge of the study at 2, 4, 6, 8 and 20 weeks in each center.

- Proportion of effective electrocardiogram (ECG) improvement.

The effective ECG improvement was defined as a standard 12-lead ECG returns to normal(or within the normal range) according to the International Society and Federation of Cardiology/World Health Organization after 20-weeks long term treatment. The ECG was performed at 0,8, and 20 weeks during treatment.

Secondary efficacy endpoints are:

- Change from baseline in weekly average frequency of self-reported angina episode over the 20-weeks treatment phase.
- Weekly average nitroglycerin consumption rate at week 8 and week 20.

Throughout the study, patients recorded the occurrence of anginal attacks and the number of nitroglycerin use on diary cards and the study staff at each clinical site reviewed the angina and nitroglycerin use cards with the patient at each study visit(2, 4, 6, 8 and 20 weeks) to ensure accuracy.

- Change from baseline in 5 dimensions of the Seattle Angina Questionnaire (SAQ) and the proportions of patients who were clinical significance at week 8 and week 20.

The SAQ is a disease-specific functional status measure that was developed to quantify the physical and emotional effects of CAD[6].Each SAQ dimension (anginal frequency, physical limitation, anginal stability, disease perception, and treatment satisfaction) was scored on a scale of 0 to 100 and the clinical significance was defined as a difference of 8 points or more on the physical-limitation scale, 25 or more on the angina-stability scale, 20 or more on the angina-frequency scale, 12 or more on the treatment-satisfaction scale, and 16 or more on the quality-of-life scale[7].Patients will complete the SAQ at 0,8, and 20 weeks.

- Change from baseline in the blood stasis syndrome and the proportion of patients who had significant syndrome improvement.

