## **11 STATISTICAL CONSIDERATIONS AND ANALYTICAL PLAN**

### **11.1 Selection of data sets**

#### **11.1.1 Efficacy analysis sets**

Full analysis set (FAS): includes all randomized patients and those without any evaluable follow-up data after randomization are excluded. For patients who did not complete the study according to the protocol, a last observation carried forward (LOCF) procedure was performed.

Per protocol set (PPS): includes all subjects in the FAS population who meet the study treatment compliance criteria and had no major protocol violations.

For primary outcome measures, statistical analyses will be performed separately in both FAS and PPS populations.

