#### **11.2 Dynamic statistical plan**

One interim analyses will be conducted under blinding conditions after 1/2 of the total number of cases have completed the trial.

Statisticians and principal investigators are responsible for drafting a written plan for statistical analysis according to the study protocol. It includes the number of included, excluded or withdrawal patients, the demographic and baseline characteristics of included patients, treatment compliance, efficacy analysis and safety analysis.

Qualitative data will be described with absolute and relative (proportion or percentage) values; and quantitative data will be summarized with mean, standard deviation, maximum, minimum, and median.

Paired t-test will be used for comparison before and after treatment within a treatment group. In analysis of variance (ANOVA) for multiple comparisons within a group, if the variances are assumed to be equal, then Student-Newman-Keuls (SNK) significance test will be used for pairwise comparison; if the variances are not assumed to be equal, then non-parametric test will be applied. Two-samples t-test will be used for comparison between treatment groups. Fourfold table will be displayed for comparison of categorical parameters: Chi-squared test for nominal categorical data and rank sum test for ordinal categorical data. Also, the analysis of covariance (ANCOVA) can be used to control for potential confounding variables.

All *P* values are two-side. Statistical significant level is set to be 0.05.

For between-group comparisons, chi-square test, Fisher's exact test, Wilcoxon rank test or Cochran-Mantel-Haenszel (CMH)  $\chi^2$  test may be used for qualitative data; while t-test, ANOVA, Wilcoxon rank test or ANCOVA may be applied for quantitative data.

**Baseline analysis:** Demographic and baseline characteristics will be reported for each subject. Comparisons between the treatment groups will be conducted using ANOVA or

Chi-square test to assess the degree to which comparability of randomization can be achieved.

**Dropout analysis:** The overall dropout rate and the dropout rate due to AEs will be compared between the treatment groups by using Chi-square test.

**Efficacy analysis:** The effect of different study sites on efficacy parameters will be considered and analyzed.

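### Two primary endpoints share a flat two-sided 0.05 level with no rule for which must succeed, and the trial is sized on only one of them

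*Protocol*

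**What the plan says.** - **Endpoints.** The Synopsis and section 6.2 both introduce the primary endpoint in the singular, "The primary efficacy endpoint of this study is", and then list two items: "Proportions of patients who were angina-free" and "Proportion of effective electrocardiogram (ECG) improvement". The second is defined as a 12-lead ECG that is normal after 20 weeks. The two are joined by neither an and nor an or, and no order of testing is given.
- **Level.** Section 11.2 says of P values: "values are two-side. Statistical significant level is set to be 0.05". The level is neither split nor ordered across endpoints.
- **Size.** Section 3.2: "we initially estimated the sample size based on one of the primary efficacy endpoints, i.e. the proportions of patients who were angina-free". The assumed rates are 30% against 20%, with 0.05, power 0.80 and 465 patients, enlarged to 576. The re-estimation to 736 reports angina-free rates only (29.17% against 20.99%). No ECG rate appears anywhere.
- **Interim.** Section 3.1 ends the trial if superiority is shown at the interim, without naming an endpoint. Section 3.2 applies Lan-DeMets O'Brien-Fleming spending.
- **Analysis sets.** Section 11.1.1: "For primary outcome measures, statistical analyses will be performed separately in both FAS and PPS populations". It does not say which set decides.

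**The concern.** With two primary endpoints, a protocol has to say what counts as success. If either endpoint is enough, two tests at 0.05 give two chances of a false positive, and the 0.05 level no longer describes the trial's error. If both are needed, the error is held, but the planned 0.80 power refers to one endpoint while success depends on two. The same data (angina-free significant and ECG not, or the reverse) could then be reported as success or failure according to a rule chosen after the results are known. Section 3.1 itself counts protection of the Type I error as part of the trial's validity.

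**Working it through.** **1. The plan's own sample size.** Inputs from section 3.2: p1 = 0.30, p2 = 0.20, level 0.05, power 0.80. Allocation is 1:1 (Synopsis). The formula is the pooled-variance comparison of two proportions without continuity correction:

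n per arm = [z_α √(2·p̄·q̄) + z_β √(p1q1 + p2q2)]² / (p1 − p2)², with p̄ = 0.25, √0.375 = 0.6124 and √0.37 = 0.6083.

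- One-sided 0.05: (1.645 × 0.6124 + 0.842 × 0.6083)² / 0.01 gives 231 per arm, 462 in total. This is close to the stated 465.
- Two-sided 0.05: (1.960 × 0.6124 + 0.842 × 0.6083)² / 0.01 gives 294 per arm, 588 in total.

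So 465 matches a one-sided test, while section 11.2 makes all tests two-sided. That is a separate matter, but it means that the stated 0.80 cannot be carried over even for angina-free. The powers below are recomputed two-sided.

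**2. If either endpoint suffices.** Assume no true difference on either endpoint and a total two-sided error of 0.05 for each. The spending function is taken to hold each endpoint's error across the two looks, and any effect of the sample-size re-estimation is set aside.

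- Independent, either direction: 1 − 0.95² = 9.75%.
- Independent, favouring XXK: 1 − 0.975² = 4.94%.
- Correlated: one minus the bivariate normal probability that neither statistic crosses 1.96.

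| Correlation of the two tests | Error in either direction | False claim for XXK |
|---|---|---|
| 0 | 9.75% | 4.9% |
| 0.3 | 9.5% | 4.8% |
| 0.5 | 9.1% | 4.5% |
| 0.8 | 7.8% | 3.9% |
| 1 | 5.0% | 2.5% |

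**3. If both must succeed.** Joint power cannot exceed the power for angina-free alone:

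Power = Φ{[(p1 − p2)√n − 1.960 √(2·p̄·q̄)] / √(p1q1 + p2q2)}, n per arm.

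For 736 evaluable (n = 368) at the design rates: (0.1 × 19.183 − 1.200) / 0.6083 = 1.18, so the power is 88.1%. At the interim rates: (0.0818 × 19.183 − 1.2015) / 0.6103 = 0.60, so the power is 72.7%.

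The last column is the square of the cap. It assumes that ECG has the same power as angina-free and that the tests are independent.

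| Evaluable N, rates | Angina-free power (cap) | Joint power, equal ECG power, independent |
|---|---|---|
| 465, design | 70.3% | 49.4% |
| 576, design | 79.3% | 62.9% |
| 736, design | 88.1% | 77.6% |
| 736, interim | 72.7% | 52.8% |

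Because no ECG rate is given, the ECG power has to be varied. At 736 and the design rates, with independence, ECG power of 50% gives 0.881 × 0.50 = 44.1%, and 90% gives 0.881 × 0.90 = 79.3%. If instead each endpoint is assumed to have exactly 80% power, joint power is 64% (independent), 69% (correlation 0.5) or 73% (correlation 0.8).

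**The case against.** **A rule may stand elsewhere.** Section 11.2 provides for a written analysis plan, which is not shown, and testing order is often placed there. That stands as far as it goes: the protocol does not prove that the trial has no rule. But the two primaries, the flat level and the single-endpoint sizing are all stated in the protocol, and the analysis plan is to be drafted from it. Two other provisions do not supply a rule. The O'Brien-Fleming spending covers repeated looks, not two endpoints. The rule in section 7.1 that the lower grade prevails when symptoms and ECG disagree grades a patient, not the trial.

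**Stronger readings that a reader might infer.**

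- *That a false claim for XXK has nearly a 10% chance.* The 9.75% needs independent tests and also counts false wins for the control. With the two-sided tests of section 11.2, the error in favour of XXK is at most 4.9%.
- *That power is well below 80% if both endpoints are required.* This needs ECG rates and a correlation, and the documents give neither. At 736 and the design rates, joint power could reach 88% with a strong ECG effect or high correlation. A shortfall is certain only at the interim rates (cap 72.7%) or at the initial numbers, two-sided (caps 70.3% at 465 and 79.3% at 576).
- *That testing in both FAS and PPS multiplies the chances of success.* Section 11.1.1 says that both analyses are run. It does not say that a PPS win is enough, and running both is ordinary practice.
- *That the interim stop could be taken on either endpoint.* The endpoint is not named, but section 3.2 puts the stopping rule in the paragraph that sizes on angina-free and reports the interim on angina-free only. The wording needs tidying; it is not evidence of a second route to stopping.

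**Conclusion.** The point holds in this form: the protocol has two primary endpoints, one unadjusted two-sided 0.05 level, no rule for success across them, and sizing and re-sizing on angina-free alone.

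- Under an either-endpoint rule, the false-claim risk for XXK goes from 2.5% to between 3.9% (correlation 0.8) and 4.9% (independence). The two-directional error goes from 5% to between 7.8% and 9.75%.
- Under a both-endpoints rule, the 0.80 target covers only one of the two requirements. The cap at 736 evaluable patients is 88.1% at the design rates or 72.7% at the interim rates. Both treat all 736 enrolled as evaluable, so dropout lowers them. Where joint power lies below the cap depends on assumptions about ECG that the protocol does not make.

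The rule needs to be fixed before the treatment codes are opened for the final analysis, because it cannot credibly be chosen afterwards.

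**What to change.** In sections 6.2 and 11.2, state a fixed sequence:

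1. Test angina-free first, at the full two-sided 0.05 under the O'Brien-Fleming spending.
2. Test ECG normalisation only if angina-free is significant, against its own spending boundary.
3. State that FAS decides and PPS is supportive.
4. State in sections 3.1 and 3.2 that the interim superiority stop is on angina-free.
5. Disclose that this order follows the endpoint used for the initial sizing in section 3.2, but is being written down after the by-arm interim angina-free rates were known.

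The change is to wording and needs no added patients for the multiplicity itself. Its price is that no confirmatory ECG claim is possible if angina-free fails.

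The alternatives cost more. Splitting the level to 0.025 per endpoint lowers angina-free power at 736 evaluable, design rates, from 88.1% to 81.5%. Requiring both needs no adjustment of the level, but reaching 80% joint power would take about 770 evaluable patients, assuming the same 30% against 20% on ECG and independent tests.
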